#### Procedure for unblinding if needed {17b}

The procedure will only be unblinded if there is an occurrence of an adverse event. The adverse event will be reported to the Joint Clinical Research Ethical Committee of the CUHK and the New Territories East Cluster of the Hospital Authority.

### Data collection and management

#### Plans for assessment and collection of outcomes {18a}

Demographic data and injury history will be collected during screening and before the recruitment. Participants who have fulfilled the eligibility criteria will be randomly allocated into the treatment groups. This is followed by the collection of the outcomes as listed in “Results” at baseline and different time points.

#### Plans to promote participant retention and complete follow-up {18b}

The office hours of the Sports Performance and Biomechanics Laboratory, Prince of Wales Hospital, will be extended to the evening to accommodate the participants’ working hours for the PEMF therapy and assessments.

#### Data management {19}

The collected data will be entered into Excel and SPSS files. They will all be password-protected and destroyed 5 years after publication in Ph.D. thesis and peer-reviewed journals. The Ph.D. student will be responsible for the data collection, data entry, and data analysis under the guidance of the biostatistician. Double data entry and range checks for data values will promote data quality.

#### Confidentiality {27}

All online data relating to the participants will be password-protected on the laboratory’s computer, and hard copies (i.e., consent forms and data sheets) will be placed in files and kept in a locked cabinet at the Sports Performance and Biomechanics Laboratory. Only the research team in charge of the study will have access to the information. Participants will not have any access to the data set. There is no plan to share the data collected with other organizations.

#### Plans for collection, laboratory evaluation, and storage of biological specimens for genetic or molecular analysis in this trial/future use {33}

There are no plans to collect any biological specimens for genetic or molecular analysis in this trial.

### Statistical methods

#### Statistical methods for primary and secondary outcomes {20a}

SPSS version 26.0 will be used to analyze the primary and secondary outcomes based on the intention to treat (ITT) principle. ITT analysis will be performed using all randomized patients, including data for those terminated or lost to follow-up. During the process, assumptions will be checked, and remedial measures will be employed. The normality of the data will first be determined using the Kolmogorov–Smirnov test or the Shapiro–Wilk test (*p* > 0.05) to test for the normality of the data distribution. Other graphical methods such as Q-Q plots or histograms will also be used for visual inspection of the distribution and to assess the normality. If skewness and heteroscedasticity are present, transformation methodology such as Logarithm may be applied to make the distribution more symmetric and stabilize the variance. Baseline data and clinical variables between both groups will be compared using independent Student’s* t*-tests (parametric)/Mann–Whitney *U* test (non-parametric) for continuous data and the χ^2^ of independence for categorical data, respectively. Descriptive statistics will be presented in either mean (SD) or frequency (%). Thereafter, a repeated measure analysis of variance (RMANOVA) will be used to measure the time/exposure effects of muscle strength, Y balance test, LSDT, SLT, DROM, and results of the questionnaire between baseline, week 4, week 8, 3rd month, 6th month, and 1-year follow-up. Analysis of covariance (ANCOVA) will be conducted for baseline characteristics and prognostic factors as covariates and compared for group differences in different time points. Repeated-measure ANOVA and ANCOVA will be applied for all participants who have completed the assessments post-treatment. Bonferroni correction will be performed for multiple comparisons. Sensitivity analysis will be conducted by comparing the results of the imputation method to complete-case and available data analyses. The significant level will be set at 0.05.

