### Trial design {8}

This is a prospective randomized, double-blind, placebo-controlled trial with two parallel groups and a 1:1 allocation ratio to investigate the treatment effects of PEMF for participants with CAI. All participants will be randomized into an intervention group (*n* = 24, active PEMF and SC) and the control group (*n* = 24, sham PEMF and SC). Researchers will perform all patient-reported outcome measures (PROM), functional, and ultrasonographic outcomes during baseline assessment, 4 weeks, 8 weeks, and follow-up visits on the 3rd month, 6th month, and 1 year after the commencement of the trial. An overview of the study is displayed in Fig. 1.

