### Sample size {14}

Using the G*Power software (Germany) [46], a sample size of 48 (*n* = 24 per group, 1:1 allocation) is calculated based on the highest attrition rate of 40% at 3rd month follow-up of the study to retain a sample size of *n* = 28, according to similar research [47]. The calculation is according to the *F* test-repeated measures ANOVA, between factors, with an effect size of 0.3, an alpha level of 0.05, (1 − *β* err prob) = 0.8 to detect a significant change of the area of COP from 42.0 (± 23.6) to 25.4 (± 8.2) [48].

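### Baseline is an outcome level in the repeated-measures ANOVA, and the trial is sized on that kind of model's group main effect; adjusting the post-baseline average for baseline gives more power from the same data

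*Protocol article*

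**What the plan says.** The article's section on statistical methods for primary and secondary outcomes {20a} states that "a repeated measure analysis of variance (RMANOVA) will be used to measure the time/exposure effects" of the listed outcomes, including the single-leg test, "between baseline, week 4, week 8, 3rd month, 6th month, and 1-year follow-up". Baseline is thus one of six repeated levels. The text does not say whether the group main effect or the arm-by-time interaction is the test of treatment.

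The sample size section {14} names the test used for planning: "test-repeated measures ANOVA, between factors, with an effect size of 0.3, an alpha level of 0.05". That is the group main effect. The number of measurements and the correlation between them are not given.

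The methods section then adds a second analysis: "Analysis of covariance (ANCOVA) will be conducted for baseline characteristics and prognostic factors as covariates", comparing the groups at the different time points. It does not say which of the two analyses is confirmatory, or that the baseline value of the outcome is among the covariates. Both analyses are applied to participants who completed the post-treatment assessments. Baseline data are also to be compared between arms by significance tests.

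**The concern.** Treatment cannot have acted before randomisation, so the baseline visit carries no information about its effect as an outcome. Its value lies in explaining variation between people, which is what a covariate does. Entered as a time level, it does the opposite. The group main effect averages five visits that may show an effect with one that cannot, and person-to-person variation remains in the denominator. The arm-by-time test escapes this dilution but asks a broad question on 5 degrees of freedom, so its power is low for a steady effect.

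The trial randomises 48 and expects to retain 28, so it has little power to spare. With two unranked analyses, the reader also cannot tell in advance which result will carry the conclusion.

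**Working it through.** **Inputs from the article:** 24 per arm; 28 retained after 40% attrition; f = 0.3 (for two groups d = 2f = 0.6); two-sided alpha 0.05; power 0.80; six levels, one of them baseline.

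**Assumed, because not given:** equal variances and equal correlation rho between any two visits; no baseline difference; a constant 0.6 SD effect at all five later visits; 14 analysed per arm.

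**The plan's own figure.** The attrition step reproduces: 28/0.6 = 46.7, hence 47, or 48 when made even. The 28 depends on inputs that are not stated. For the between-groups test the noncentrality is f² × N × m / (1 + (m − 1) × rho). With m = 6 and rho = 0.5 this is 0.09 × 28 × 6 / 3.5 = 4.32, giving 51.7% power; 80% needs N = 54. With m = 6, N = 28 gives 80.1% at rho of about 0.156, so that value is included below.

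**Group main effect over six levels.**
- Effect: (5/6) × 0.6 = 0.5 SD.
- Variance of a person's mean: (1 + 5 rho)/6. At rho 0.5 this is 0.583.
- Noncentrality at rho 0.5: 0.5/√(4 × 0.583/28) = 1.73 on 26 df, power 38.5%.

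**Mean of five post-baseline visits, adjusted for baseline.**
- Effect: 0.6 SD.
- Residual variance: (1 + 4 rho)/5 − rho². At rho 0.5 this is 0.35.
- Noncentrality at rho 0.5: 0.6/√(4 × 0.35/28) = 2.68 on 25 df, power 73.2%.

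**Arm-by-time interaction.** Noncentrality (28/4) × 0.36 × (5/6)/(1 − rho). At rho 0.5 this is 4.2 on 5 and 130 df, power 29.4%.

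**Single-visit ANCOVA.** Effect 0.6 SD, variance 1 − rho².

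| rho | Main effect, 6 levels | Adjusted mean of 5 visits | Interaction, 5 df | Single-visit ANCOVA | Information ratio, adjusted mean to main effect |
|---|---|---|---|---|---|
| 0.156 | 64.7% | 79.5% | 18.2% | 34.0% | 1.4 |
| 0.3 | 50.5% | 73.2% | 21.4% | 36.0% | 1.7 |
| 0.5 | 38.5% | 73.2% | 29.4% | 42.2% | 2.4 |
| 0.7 | 31.3% | 83.5% | 48.1% | 57.0% | 4.0 |

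The total N for 80% power, main effect against adjusted mean, is 56 against 34 at rho 0.3, 76 against 34 at 0.5, and 98 against 26 at 0.7. If all 48 are analysed at rho 0.5, the powers are 60.3% and 93.0%. Single-visit ANCOVA overtakes the main effect only above rho of about 0.46.

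**Sensitivity to effect size (N = 28).**
- If f = 0.3 is already the six-level average, the post-baseline effect is 0.6 × 6/5 = 0.72 SD. The powers are 80.1% against 91.6% at rho 0.156, and 51.7% against 87.2% at rho 0.5.
- The sample size section's centre-of-pressure figures, 42.0 (23.6) and 25.4 (8.2), give a pooled SD of √((23.6² + 8.2²)/2) = 17.67 and d = 16.6/17.67 = 0.94, which is f = 0.47 and not the stated 0.3. With d = 0.94 the powers at rho 0.5 are 74.3% against 98.1%.

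**Sensitivity to a fading effect (N = 28, rho 0.5; 0.6, 0.6, 0.3, 0.15 and 0 SD at the five visits).** Main effect 15.1%, adjusted mean 29.5%, interaction 36.9%, week-8 ANCOVA 42.2%. The main effect is the weakest of the four.

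**The case against.** The strongest reply is that baseline adjustment is already planned, and that ranking models and listing covariates is commonly left to a fuller document. The first part is true: a reader might infer that the plan has no baseline-adjusted analysis, and that would be wrong. The second part has force as regards covariate lists. It does not reach the two choices the article does fix, namely baseline as an outcome level and sizing on the between-groups effect.

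A second reply is that the article never says the main effect will carry the conclusion. This also stands; that test is named only for sizing. The arm-by-time reading is open and is not diluted by the baseline level, but its power for a constant effect is low at the correlations most favourable to the main effect and reaches only 48.1% at rho 0.7.

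A third reply is that the gain depends on the contrast and on a correlation the article does not give. This limits the point most. A reader might infer that any baseline-adjusted test beats the main effect. It does not: at rho 0.3 a single-visit ANCOVA has 36.0% power against 50.5%.

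Finally, a reader might suspect that the baseline significance tests will be used to pick covariates. The article compares baseline data and separately names covariates, and nothing links the two.

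**Conclusion.** The point holds as a matter of efficiency and clarity. Entering baseline as a time level costs power in the test used for sizing, and the adjusted post-baseline mean did better at every correlation tried: by 1.4 times the information at rho 0.156, 1.7 at 0.3, 2.4 at 0.5 and 4.0 at 0.7. These ratios rest on equal correlation and a constant post-baseline effect; the powers rest also on 0.6 SD and 28 analysed. A fading effect lowers the power of the averaged contrast, and with the pattern shown a week-8 ANCOVA or the interaction does better, so the question the trial wants answered must settle the choice of contrast.

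It does not follow that the planned ANOVA is invalid. With no treatment effect, the expected group difference is zero with or without the baseline level. The loss is in power, and in a main-effect estimate that is 5/6 of a constant post-baseline effect.

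**What to change.** Name one confirmatory model for the primary outcome: the five post-baseline visits as outcomes, the baseline value of the same outcome as covariate, and terms for arm, visit and arm-by-visit. Test the single-df arm difference averaged over the post-baseline visits. Do not enter baseline as a time level, and label the other analysis as supportive.

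If one visit is the clinical target, test that visit's baseline-adjusted difference and quote its own power (36.0%, 42.2% and 57.0% at rho 0.3, 0.5 and 0.7 under the assumptions above), not that of the average.

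In the sample size section, restate the calculation for the chosen test, with the number of measurements, the assumed correlation and a range around it. Replace the between-arm baseline tests with descriptive tables.

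The cost is wording and one recalculation. The outcomes section already schedules a baseline measurement of every primary and secondary outcome, so no participants, visits or measurements are added.

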**Methods:**

This is a prospective, randomized, double-blind, placebo-controlled trial. A total of 48 adults with chronic ankle instability will be recruited and randomly allocated into either the intervention or control groups. The intervention group (*n* = 24) will receive active pulse electromagnetic field therapy and standard exercise training, while the control group (*n* = 24) will receive sham pulse electromagnetic field therapy and standard exercise training for 8 weeks. Primary and secondary outcomes will be evaluated at baseline, week 4, 8 as well as at 3-, 6-, and 12-month follow-up visits.

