#### Methods in analysis to handle protocol non-adherence and any statistical methods to handle missing data {20c}

Intention to treat analysis will be deployed to include all study participants regardless of their treatment allocation and whether the intervention for them has been completed. Regardless of the adherence to the intervention or withdrawal, they will be recorded by the Ph.D. student weekly. Missing data will be checked, and multiple imputations and sensitivity analysis will be employed assuming that the missing data are random.

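### The main models are assigned two incompatible analysis sets, all randomised and completers only, and nothing says which gives the primary result

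*Protocol article*

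**What the plan says.** Section {20a} of the protocol opens with the intention-to-treat principle for primary and secondary outcomes and defines the set: "ITT analysis will be performed using all randomized patients, including data for those terminated or lost to follow-up". It then names repeated-measures ANOVA over six time points, from baseline to 1 year, and ANCOVA for group differences at the different time points. Next it fixes who enters them: "Repeated-measure ANOVA and ANCOVA will be applied for all participants who have completed the assessments post-treatment". Shortly afterwards it describes the sensitivity work: "Sensitivity analysis will be conducted by comparing the results of the imputation method to complete-case and available data analyses".

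Section {20c} returns to the analysis set: "Intention to treat analysis will be deployed to include all study participants regardless of their treatment allocation", whether or not the intervention was completed. On missing values it says: "Missing data will be checked, and multiple imputations and sensitivity analysis will be employed assuming that the missing data are random".

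The sample size section {14} starts from "the highest attrition rate of 40% at 3rd month follow-up", taken from similar research, and plans to retain 28 of the 48 randomised.

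**The concern.** The set of participants in the primary analysis is stated twice, and the statements exclude each other. Someone lost to follow-up belongs to the set in the first statement and is removed by the second. This is not detail left to a later analysis plan: any such plan would have to break one of the two sentences.

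Two things are at stake. First, following the completers sentence gives a main result that is not intention to treat. Randomisation no longer protects the comparison if the reasons for leaving are related to outcome and differ by arm. Second, leaving the conflict in place allows the choice of set to be made once data are available. Under {16c} the allocation is revealed to the research team for analysis when the intervention ends, while follow-up runs to 1 year. Under {19} the same student collects, enters and analyses the data, with guidance from the biostatistician.

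**Working it through.** **1. The statements side by side**

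| Place | Who is analysed | Role given |
|---|---|---|
| {20a}, opening | all randomised, including those lost | primary and secondary outcomes |
| {20a}, after the models | completers of post-treatment assessments | repeated-measures ANOVA and ANCOVA |
| {20a}, sensitivity sentence | complete cases and available data | comparators for imputation |
| {20c} | all participants, with multiple imputation | intention-to-treat analysis |

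Rows 1 and 4 agree. Row 3 fits them, because it treats complete-case analysis as a comparator. Row 2 conflicts with all three: it attaches the completer set, without qualification, to the main models.

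**2. The protocol's own attrition step**

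Inputs from {14}: 28 to be retained, 40% attrition, 48 randomised.

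- Inflation: 28 / (1 − 0.40) = 46.7, so 47, and 48 for two equal groups. The stated 48 is reproduced.
- In reverse: 48 × 0.60 = 28.8 retained and 48 × 0.40 = 19.2 lost.
- With 28 kept: 48 − 28 = 20 excluded, and 20 / 48 = 41.7%.

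**3. What the completers rule could exclude**

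The rule does not say which assessments must be complete.

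- If it means every visit in the repeated-measures ANOVA, the protocol's maximum attrition gives up to about 20 of 48. Classical repeated-measures ANOVA also drops anyone with one missing visit.
- If it means week 8, when treatment ends, no attrition is given for that visit. Assuming it does not exceed the stated maximum, the loss is 0 to 40%, or 0 to about 20 people.

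**4. Illustrative bias**

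All settings here are assumptions, except the sample size and the 40%. Trials of 24 per arm were simulated with no true effect, a correlation of 0.5 between visits and 40% lost in each arm after week 4. Where loss depends on outcome, the log-odds of leaving change by 1 per SD of week-4 centre-of-pressure area. ANCOVA adjusted for baseline was run at month 3 on completers.

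| Dependence of loss on week-4 outcome | Completer bias (size) |
|---|---|
| equal in both arms | about 0 |
| in one arm only | about 0.08 SD |
| opposite in the two arms | about 0.17 SD |

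Type I error was about 5% in the first case, 5.3% in the second (2,000 trials, not distinguishable from 5%) and about 7% in the third. An estimate that also uses the week-4 outcome of those who left was within about 0.01 SD of zero in the two cases with unequal dependence. The direction of the bias depends on which arm loses which participants.

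**The case against.** The best defence is that imputed intention to treat is plainly what was meant. Section {20c} names multiple imputation, and {20a} makes complete-case analysis a comparator for it. On that reading one stray sentence conflicts with an otherwise sound plan. Much of this stands: the right method is already in the document, which is why the fix is small. It does not remove the conflict, because no sentence calls the imputed result primary and the completers sentence is unqualified.

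A reader might infer several stronger points that the documents do not support.

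- *That about 40% will be dropped.* The 40% is the highest rate assumed for planning, at month 3. It is not a stated loss for the completer set.
- *That completers will give a bias of 0.17 SD.* That needs opposite dropout mechanisms in the two arms, and nothing in the protocol suggests them. With a sham device, no sensation from treatment, and blinded participants and assessors during treatment, equal dependence is a natural null case, and its bias is about 0. Some difference between arms remains possible, for example through the withdrawal of participants with adverse events under {22}.
- *That data from early visits are thrown away.* Imputation and the available-data analysis can both use week-4 and week-8 values.
- *That the sensitivity analyses fail because none tests the missing-at-random assumption.* The protocol does not claim that they do, and a departure-from-random analysis is commonly left to an analysis plan.

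**Conclusion.** The protocol is wrong as written on who enters the main models. The contradiction rests on the text alone and needs no assumption.

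Its size does need assumptions. Up to about 20 of 48 could be excluded if the stated maximum attrition occurs and completion means all visits. The range is 0 to 40% if completion means week 8. The bias is conditional: about 0.08 SD if dropout follows outcome in one arm only, and about 0 if it does so equally in both, under the simulation settings above. These figures show that the choice of set can matter. They do not predict what this trial will see. Nor is power the argument, since the sample size was planned for 28 retained.

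**What to change.** Delete the completers sentence from {20a}. In its place, state that the primary analysis includes all 48 randomised participants in their allocated arm, using the multiple imputation already planned in {20c}, with week-4 and week-8 outcomes in the imputation model. A likelihood-based mixed model for repeated measures is an acceptable alternative, but the defect does not require it. Label the completer and available-data analyses as sensitivity only, and say which visits a participant must have attended to count as a completer.

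The cost is a change of wording and slightly more analysis work. No new data are needed. The change should be made before allocation is revealed to the research team.

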##### The elasticity of the peroneal muscle

In addition, the shear elastic modulus of a muscle will be measured using ultrasonic shear wave elastography (Aixplorer, Supersonic Imagine, France) with a linear array probe. The region of interest (ROI) will be set near the center of each muscle. The analysis area will be a 5-mm diameter circle at the center of ROI. The shear elastic modulus will be measured three times per muscle, and the average of the three measured values will be used for further analysis. The shear elastic moduli of the PL and PB will be measured at proximal 25% from the head of the fibula to the lateral malleolus. For each Q-box, the maximum, minimum, and mean (in kPa) of the stiffness of the muscle are measured [41].

Other patient-reported outcome measures (PROM) will be employed to assess overall health and foot and ankle-related symptoms, pain, physical activity level, and health-related quality of life. Foot and Ankle Ability Measure (FAAM) will be used to assess the foot and ankle functional limitations among CAI individuals. The FAAM consists of 29 items, scored between 0 and 4, divided into two subscales: activities of daily living (21 items) and sports (8 items) [42]. For score analysis, the percentage of each subscale is used separately. According to the International Ankle Consortium, values of the day living activities < 90% and < 80% of the sports subscales of the FAAM score were considered unsatisfactory. Manchester-Oxford foot and ankle questionnaire (MOXFQ) is a 16-question self-reported score designed to evaluate the impact of foot and ankle problems on a person’s quality of life. The dimensions comprise 3 subscales: walking/standing problem (7 items), foot pain (5 items), and issues related to social interaction (4 items). After that, all three domains of the MOXFQ can be summed up and converted to a metric from 0 to 100 to create a summary index score (MOFXQ index) [43]. The pain score will be evaluated using the visual analog scale (VAS) ranging from 0 to 100. For the pain score, the higher the score indicates, the more severe the pain. The Short Form-36 questionnaires (SF-36) will be used to evaluate the health-related quality of life [44]. The International Physical Activity Questionnaire will be used to evaluate the physical activity levels [45]. All primary and secondary outcomes will be evaluated at baseline, 4th week, 8th week, 3rd month, 6th month, and 12th month follow-up.

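### Single-step Bonferroni is valid here, but Holm's step-down procedure gives the same error control and is never less powerful: a cheap improvement for the visit-wise comparisons

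*Protocol article*

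**What the plan says.** Section {20a} of the protocol article plans a repeated measures ANOVA "between baseline, week 4, week 8, 3rd month, 6th month, and 1-year follow-up" and an ANCOVA in which the arms are "compared for group differences in different time points". On multiplicity it has one sentence: "Bonferroni correction will be performed for multiple comparisons". It then adds: "The significant level will be set at 0.05". It does not state the family of tests, their number or whether they are two-sided.

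The end of the outcomes section gives the visits: "All primary and secondary outcomes will be evaluated at baseline, 4th week, 8th week, 3rd month, 6th month, and 12th month follow-up". Every outcome therefore has five post-baseline visits at which the arms can be compared.

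The sample size section {14} rests on one test, specified as "repeated measures ANOVA, between factors, with an effect size of 0.3, an alpha level of 0.05, (1 − *β* err prob) = 0.8". It starts from 48 participants, 24 per arm, and allows for the "highest attrition rate of 40% at 3rd month follow-up of the study to retain a sample size of *n* = 28".

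**The concern.** Bonferroni in its usual single-step form holds every comparison in a family to the same strict threshold, however many of the others have already been rejected. Holm's procedure starts at that threshold and relaxes it after each rejection. It needs no extra assumption, in particular none about the correlation between visits.

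This matters more in a small trial whose background section asks about effects in both the short and the long term. A sustained benefit would be shown by differences at several visits, and that is the case in which a step-down procedure helps. With 24 per arm, and perhaps 14 per arm retained, power at single visits is scarce. What is at stake is some power for the second and later visit-specific findings. The validity of the analysis is not at stake.

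**Working it through.** **Inputs from the protocol article.** Level 0.05; five post-baseline visits; 24 per arm randomised, 28 in total retained (14 per arm); effect size f = 0.3; COP area 42.0 (SD 23.6) against 25.4 (SD 8.2).

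**Assumptions.** One family of m = 5 PEMF-versus-sham tests per outcome; two-sided tests; equal correlation between visits of 0.5 or 0.8; two-sample t-tests in place of ANCOVA.

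**1. The plan's own figure.** 28 / (1 − 0.40) = 46.7, so 47, or 48 with equal arms. The inflation reproduces. The 28 itself depends on the number of measurements and their correlation, which are not given: with f = 0.3 and power 0.8, six measurements at correlation 0.15 or five at 0.1 give 28, while six at 0.5 give 54. It can be neither confirmed nor refuted. It comes from a single F test at 0.05, so the choice between Bonferroni and Holm does not enter it.

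**2. Thresholds for m = 5.** Bonferroni: 0.05/5 = 0.01 for every test. Holm, on ordered p-values: 0.05/5 = 0.01, 0.05/4 = 0.0125, 0.05/3 = 0.0167, 0.05/2 = 0.025, 0.05/1 = 0.05, stopping at the first failure.

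**3. Why Holm is never worse, for any m.**
- Every Holm threshold is at least 0.05/m, so any p-value that passes Bonferroni also passes Holm.
- Suppose m0 hypotheses are truly null. When the first of them is rejected, at least m0 hypotheses are still in play, so the threshold is at most 0.05/m0. The chance that any of the m0 null p-values falls that low is at most m0 × 0.05/m0 = 0.05, whatever the correlation.

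**4. Effect sizes.** For two equal arms d = 2f = 2 × 0.3 = 0.6. From the COP figures, pooled SD = √((23.6² + 8.2²)/2) = 17.67 and d = (42.0 − 25.4)/17.67 = 0.94, if they are read as a contrast between arms. A value of 0.8 lies between.

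**5. Simulated power** at the visits with a real effect, in %, Bonferroni → Holm (correlation 0.5, 20,000 trials per setting):

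| Per arm | d | Real at 1 visit | Real at 2 visits | Real at all 5 |
|---|---|---|---|---|
| 24 | 0.6 | 28.2 → 28.2 | 28.0 → 29.1 | 28.4 → 34.8 |
| 24 | 0.8 | 53.4 → 53.5 | 54.0 → 55.6 | 53.4 → 63.6 |
| 24 | 0.94 | 71.6 → 71.7 | 71.0 → 72.8 | 71.0 → 81.2 |
| 14 | 0.6 | 14.0 → 14.1 | 13.9 → 14.4 | 13.7 → 16.7 |
| 14 | 0.8 | 27.8 → 27.9 | 28.3 → 29.4 | 27.6 → 34.2 |
| 14 | 0.94 | 40.9 → 40.9 | 40.1 → 41.6 | 40.2 → 49.2 |

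Within a row the Bonferroni values differ only by simulation noise. At correlation 0.8 the gains are 0 to 0.1, 0.7 to 1.7 and 3.8 to 9.1 points.

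**6. What does not change.** Holm's first step is the Bonferroni test, so the chance of at least one significant visit is identical. For 24 per arm, d = 0.8, correlation 0.5 and all visits real it is 86.1% under both.

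**7. Error rates.** With no effect at any visit (24 per arm, correlation 0.5) the family-wise error is 4.4% under both. With two real visits at d = 0.94 it is 2.7% under Bonferroni and 3.7% under Holm. Both stay below 5%.

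**The case against.** The strongest reply is that this is a preference between two valid methods. Bonferroni is prespecified, holds under any correlation and conflicts with no other part of the article. No power is claimed for individual visits. All of that stands, and it is why the point is an improvement only.

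The gain is also largest in a favourable case. If the effect is confined to one visit, Holm adds essentially nothing. Unequal effects show the same dependence on assumptions. For an assumed effect at all five visits that fades (d = 0.6, 0.9, 0.8, 0.6, 0.5; correlation 0.6), power at month 12 rises from 18% to 29% with 24 per arm, but only from 9% to 14% with the 14 per arm that the sample size section plans to retain. The article does not state such a profile.

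Bonferroni does buy something in return. It comes with simple simultaneous confidence intervals that match its tests, and it is stricter at the null visits when other visits carry real effects. The first advantage is theoretical here, because {20a} does not promise such intervals. The second is strictness beyond the 0.05 that the plan asks for.

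A reader might go further and infer that Bonferroni is a mistake, or that it makes the trial miss real visit differences with nothing gained. The documents do not support either reading. The method is valid, the chance of a first significant visit is the same under both, and the possible loss ranges from nil to moderate.

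**Conclusion.** The point holds as a cheap improvement. Holm's dominance does not depend on any assumption about the family, the correlation or the effect. Its size does. With five visit-wise tests per outcome, d from 0.6 to 0.94, 14 or 24 per arm and equal effects at the affected visits, per-visit power rises by about 0 to 2 points when one or two visits are affected and by about 3 to 10 points when all five are.

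The d of 0.94 also assumes a contrast between arms; the sample size section may instead be describing a change over time. That the family is left undefined is not part of this point, since an analysis plan that is not shown may settle it.

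**What to change.** Replace the Bonferroni sentence in {20a} by:

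> Within each family of PEMF-versus-sham comparisons, p-values will be adjusted by Holm's step-down procedure (family-wise two-sided 0.05); 95% confidence intervals will be reported and labelled as unadjusted for multiplicity.

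In practice, take the unadjusted p-values from SPSS, sort them and compare them in turn with 0.05/m, 0.05/(m − 1), …, 0.05, stopping at the first that fails.

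The cost is one sentence and a spreadsheet step in place of the SPSS Bonferroni option. It needs no further participants or data. The downside is that an unadjusted interval can exclude zero while the Holm-adjusted p-value exceeds 0.05, so the label is needed. The change should be recorded before the allocation is disclosed to the research team, which section {16c} sets at the end of the intervention; a later switch could look data-driven.
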